## RANDOMIZATION

A stratified block randomization will be used to assign the townships into 4 groups: high CVD risk management package only, salt reduction only, both package and salt reduction, and usual care (neither). Randomization will be stratified by county. In each county, the 12 townships will be divided into 3 blocks according to geographic proximity. In each block, the 4 townships will be randomly assigned to receive both interventions, either intervention, or neither. For the entire study, there will be 60 townships with ‘package’ and 60 townships with ‘no package’ (with or without salt reduction) and 60 townships with ‘salt reduction’ and 60 townships with ‘no salt reduction’ (with or without “package intervention”). There will be 30 townships receiving both the package and the salt reduction interventions, 30 receiving package only, 30 salt reduction only, and 30 receiving neither interventions. All groups will receive the usual care.

## INTERVENTION AND CONTROL

INTERVENTION

For the package intervention, the period of intervention will be 2 years; and for the salt reduction, approximately 1.5 years due to the staged onset of the two interventions.

### ‘Package’ intervention

The intervention package will be based upon the application of the core strategies described in the national practical guidelines for hypertension and cardiovascular disease management at grass-root levels in China, with further adaptation to ensure the interventions are feasible and affordable in rural China. Broadly the package will encourage the opportunistic identification of a set of high-risk individuals and then seek to improve their clinical management through the application of simplified guidelines and a defined follow-up schedule. The package will focus attention on patients considered at high cardiovascular risk on the basis of their falling into one of the following three groups, regardless of current medication use:

- Physician-diagnosed history of coronary heart disease, ischemic stroke, or hemorrhagic stroke, or
- Older age (50 years or older for men; 60 years or older for women – “50+/60+” hereafter) and having physician-diagnosed Type I or type II diabetes
- Older age (50+/60+) and SBP 160 mmHg (note that for simplicity, DBP is not included in the criteria)

Details of the interventions are in Appendix 1. Briefly,

- Implementing the CVD risk management package: Village doctors will screen, classify, treat, and follow-up high-risk cardiovascular patients according to the Package. A flow chart summarizing the main points and procedures will be designed as a wall poster and distributed to all doctors in the intervention group as an aid to help them adhere to the Package (see Appendix 1-A).
- Training on package: The training of the Package will be provided to all the participating village doctors in the intervention group. A cardiologist from each county hospital (10 in total) will be trained centrally in Beijing in both the package itself as well as how to be a trainer. The county hospital cardiologists will then train all village doctors in the intervention villages in their county. This “train the trainers” model is being used since it best emulates the practicalities of how the program might be rolled out if it would be proved effective. All village doctors can only begin intervention after they pass the training examination.
- The village doctors will also be trained and asked to complete a simple case management record (see Appendix 1-B for a sample record) documenting the initial clinical visit and each subsequent follow-up visit for all high-risk patients identified.
- Digitized central database and performance feedback: We will establish a central database and management system in Peking University Clinical Research Institute. An independent monitor will be appointed in each county to perform study quality control and to digitize all case management records every 2 months and upload the data via a secure network to the central database. Village doctors will be provided with regular semi-yearly performance feedback on key performance indicators (see Appendix 1-C) generated by the central database to reinforce their compliance to the package.
- Economic incentive: Observed performance will also determine the additional performance-based provider payments made to the village doctors with specific sums allocated for the achievement of specific clinical goals, especially preventive care that they are not normally compensated for such as blood pressure measurement, regular follow-up, lifestyle recommendations, and hypertension control (the last column of Appendix 1-C includes details on how the village doctors will be paid). The frequency of these payments will be the same as performance feedback – once in half a year.

### ‘Package’ control

Villages in the control group will continue their usual practices without the introduction of the ‘package’.

### ‘Salt reduction’ intervention

The salt reduction intervention will be a multi-faceted program including general community health education, specific targeting of patients at high risk of blood pressure-related disease (those targeted by the package) and a food supply measures designed to promote the sale of salt substitute through the village and township convenience stores.

The community-wide education component will seek to tap into the mechanisms already established in the villages for the dissemination of health information, such as township and village radio and TV broadcast system, public announcement system, bulletin boards in the village offices or village clinics, and promotional pamphlets. This will require the active engagement of the village council and the primary health care provider who will be informed and trained by county level public health experts. These county level staff will in turn be trained by central study staff under the same ‘train the trainer’ model used for the implementation for the ‘package’. The community-wide education will include verbal counselling in small groups, public meetings, visual aids and other mechanisms throughout the two-year intervention period. Specific advice will be given to reduce the quantities of salt added to food during cooking, to limit the amount of salt pickled foods eaten, and to soak salt cured meats in water overnight prior to eating them.

The component targeting the high-risk individuals will be delivered primarily by the village health care providers as part of an expanded chronic disease prevention role. Healthcare providers will be trained to opportunistically screen adult patients presenting for any reason by asking simple questions about disease history and making blood pressure measurements where possible. If a patient is identified as possibly falling into the high risk group they will be given particular encouragement to reduce salt intake and informed about the merits of replacing their salt supply with salt substitute. Community health educators may work alongside village doctors to hold special group counselling sessions for high-risk patients and to conduct home visits to demonstrate how to cook low-salt and tasty dishes.

Finally, there will be a concerted effort to make salt substitute available for sale in all village and township stores in the intervention areas. This will be a low-sodium, high-potassium salt-substitute (consisting of 65% sodium chloride, 25% potassium chloride and 10% magnesium sulphate) and the villagers will be encouraged to use the salt substitute to replace all household salt use (cooking, pickling and discretionary mealtime use). Contacts in the relevant Provincial salt manufacturing corporations will be used to ensure a supply of salt substitute and if possible the salt substitute will be subsidized such that it is the same price as or lower price than usual salt.

### ‘Salt reduction’ control

Villages in the control group will continue their usual practices without the introduction of any salt reduction initiatives.

## OUTCOMES

The primary outcomes will be the same for the package intervention and the salt reduction intervention, which is the mean blood pressure changes between the groups..

The primary outcome for the package intervention will be mean blood pressure level of high-risk patients.

The primary outcome for the salt reduction intervention will be mean blood pressure level of older adults (50+/60+).

### Secondary outcomes for the package intervention

- The proportion of high-risk individuals in the village that are identified and regularly managed by the village doctors. Regular management is defined as visiting the village doctor at least once a month, at least 9 times in a year, and measuring blood pressure and prescribing cardiovascular medicine during each visit
- The proportion of high-risk individuals who had visited the village clinic and received pharmaceutical treatment from the village doctor at least once in the past year
- The proportion of high-risk individuals that are treated with a blood pressure lowering agent
- The proportion of high-risk individuals that are treated with aspirin
- The proportion of high-risk individuals that have systolic blood pressure controlled to less than 140mmHg
- The proportion of high-risk individuals that report having received therapeutic lifestyle changes recommendations from the village doctors
- The mean blood pressure level of older adults (50+/60+) in the village
- The proportion of older adults with hypertension (systolic blood pressure >=140 mm Hg)

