We conducted another randomized double-blind controlled trial on salt substitute among 220 hypertensive patients and their 348 family members in rural Beijing from 2005-2006. After the one-year intervention, systolic blood pressure reduced by 4.1 (0.8, 7.4) mmHg (measured clinically), 3.1 (0.4, 5.8) mmHg (measured by home monitoring), and 2.4 (-2.4, 5.7) mmHg (ambulatory monitoring) respectively. Among family members, systolic BP by home monitoring reduced by 1.5 (-0.4, 3.4) mmHg, of which family members with hypertension had a reduction of 2.7 (-1.9, 7.2) mmHg and with normal blood pressure, only 0.5 (-1.2, 2.1) mmHg. Reduction in systolic BP was bigger with older age. Further analysis showed that withdrawal from medication was more pronounced in the salt substitute group than control group (normal salt), reaching statistical significance by the 3rd month (p<0.05). During the trial, all (100%) people in the salt substitute group reported consuming the salt provided to them “all” or “most” of the time and 98.2% of the participants in the control group (normal salt) reported so. No between-group difference in compliance was detected (p>0.05).

A similar 3-month randomized single-blind trial conducted in Tibet in 2009 among 284 hypertensive patients showed a bigger reduction [-8.8 mmHg (95% CI: -19.6 to -1.0) systolic and -4.5 mmHg (95% CI: -8.5 to -0.6) diastolic respectively] in this high-altitude area with very high prevalence of hypertension and higher average baseline blood pressure level.

There is currently significant interest in the potential for salt substitutes to decrease vascular disease in China and in Beijing there is a directive requiring greatly increased sales of salt substitute by the Beijing Salt Corporation. Against this background there is a high likelihood that it will be possible to make salt substitute more widely available in rural China and this will be a core component of the salt reduction program.

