### Secondary outcomes for the salt reduction intervention

- The proportion reporting efforts to reduce salt consumption
- The proportion with hypertension
- Mean 24-hour urinary sodium excretion (based on a sub-sample)
- Average daily per capita salt sale volume in the village estimated from salt sale records in the village convenience stores

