**Chief Complaints:**

| **Medical History** |
| --- |
| 1. Does pt have any one of the following diseases (diagnosed in county / higher-level hospitals)？   **CAD**□Yes□No; **Hemorrhagic stroke**□Yes□No; **DM**□Yes□No; **Ischemic stroke**□Yes□No |
| 1. Medications the patient was taking everyday in the past 2 weeks (please record the **name**, **dosage** taken each time, and **times** taken each day, e.g. “Hydrochlorothiazide 12.5mg qd”; if no medication meets the above criteria, please record “NA”). |
| 1. Other medical histories that need to be recorded: |
| **Life Styles** |
| 1. Does the patient take measures to reduce dietary sodium aggressively in everyday life?   □Yes (e.g. do not eat pickled vegetables at all; no MSG and add minimal amount of salt when cooking dishes; unable to eat when the meal is salty.)  □Not so aggressively (e.g. eat some pickled vegetables; take care to reduce salt added in cooking; eat less when the meal is salty.)  □No (e.g. do not pay attention to the amount of salt in food at all.)   1. Is the patient a current smoker？ □Yes □No   If “Yes”, does the patient think about quitting smoking？ □Yes □No   1. Does the patient exercise regularly？(e.g. farming, walking, climbing, etc.)   □Almost everyday □3-5 time/week □1-2 times/week □almost no activities/week |
| **Physical Examination** |
| 1. Blood Pressure (SBP/DBP): / mmHg (This time)   (Optional: / mmHg (Last time), Date: / / (yy/mm/dd)   1. Height: cm; weight: kg; other signs: |
| **Prescription** |
| 1. Referral □Yes □No |
| 1. Therapeutic lifestyle changes (advise the patient to take actions to):   **Reduce salt intake** □Yes □No; **Quit smoking** □Yes □No; **Avoid binge drinking** □Yes □No  **Be physical active** □Yes □No **Control weight** □Yes □No; |
| 1. Pharmaceutical treatment (please record the **name** of the drug, **dosage** taken each time, and **times** taken each day, e.g. “Hydrochlorothiazide 12.5mg qd”; if no drug is prescribed, please record “NA”):   Doctor’s Signature: |

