| C.6 During the past 12 months, did you see your village doctor once a month?  □1. Yes  □0. No | | | | | | | | | C.7 Does your village doctor measure your blood pressure during visits?  □1. Never see village doctor  □2. Never measure  □3. Sometimes(occasionally)  □4. Almost every time  □5. Every time | | | | |
| **Physical examination (PE.2). Blood pressure and heart rate measurement (2nd)** | | | | | | | | | | | | | |
| PE.2.1 Blood pressure（Systolic/Diastolic）  PE.2.1.1**□□□**/ F.1.2**□□□** mmHg | | | | | | PE.2.2 Heart rate:  PE.2.2.1**□□□**/minute | | | | | | | |
| **Physical examination (PE.3). Body height and weight measurement** | | | | | | | | | | | | | |
| PE.3.1 Height **□□□.□** cm | | | | | | PE.3.2 Weight **□□□.□**kg | | | | | | | |
| | **CL．CVD high-risk patient confirmation checklist (CL) by the interviewer** | | | --- | --- | | CL.1 Have confirmed diabetes（C.1.1 answer Yes） | □1.Yes □0.No | | CL.2 Have confirmed stroke（C.2.1 answer Yes） | □1.Yes □0.No | | CL.3 Have confirmed CHD（Both C.3.1 and C.3.2 answer Yes） | □1.Yes □0.No | | CL.4 Have reported SBP at older age ≧ 160mmHg （C.5.1） | □1.Yes □0.No | | CL.5 Twice systolic measurements ≧160mmHg （PE.1.1 and PE.2.1） | □1.Yes □0.No | | **If any of the above is ticked YES, go to D section; otherwise, end survey** | | | | | | | | | | | | | | | |
| **D. Medication use and medical care (high-risk patients ONLY)** | | | | | | | | | | | | | |
| D.1 When was the last time that you saw your village doctor for your heart disease, stroke, diabetes or hypertension problem(s)? days ago  During that visit, did village doctor provide the following recommendations?  D.1.1 Reduce salt intake □1.Yes □0.No  D.1.2 Quit smoking □1.Yes □0.No  D.1.3 Avoid binge drinking □1.Yes □0.No  D.1.4 Be physically active □1.Yes □0.No  D.1.5 Control weight □1.Yes □0.No | | | | | | | | | | | | | |
| D.2 During the past 12 months, due to your heart disease, stroke, diabetes or hypertension problem(s)  D.2.1 How many times have you been in hospital?  （if no，go to D.3）  D.2.2 How many days have you been in hospital?  D.2.3 How much have you spent for hospitalization? RMB | | | | | | | | | | | | | |

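### The survey questionnaire has no item for the salt-effort secondary outcome and cannot score regular management to its definition in the same way in both arms

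*Protocol*

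**What the plan says.** Two secondary outcomes are at issue.

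- **Salt program** (Protocol, Secondary outcomes for the salt reduction intervention): "The proportion reporting efforts to reduce salt consumption". No denominator is given. I read it as the surveyed older adults, the population of the salt program's primary outcome.
- **Package** (Protocol, Secondary outcomes for the package intervention): the proportion of high-risk individuals identified and regularly managed. "Regular management is defined as visiting the village doctor at least once a month, at least 9 times in a year", together with "measuring blood pressure and prescribing cardiovascular medicine during each visit".

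Outcomes Evaluation names case management records as a package-only source and requires outcome assessment to be identical in all villages, whatever their assignment. The survey instrument is Appendix 2, titled for both the baseline and the follow-up survey. Its only item on visit frequency is C.6, answered yes or no: "During the past 12 months, did you see your village doctor once a month". The case management record (Appendix 1-B) asks, with three answer levels, "Does the patient take measures to reduce dietary sodium aggressively in everyday life". That record is kept for high-risk patients in the 60 package villages.

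**The concern.** An analysis plan can choose a model or a proxy, but it cannot recover an answer that was never asked for. If the form is used as printed, one listed salt outcome has no survey data. The leading package secondary outcome would have to rest on a proxy, or on a source that only one arm has.

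A case-record numerator in package villages set against a survey answer in control villages would mix the package effect with the difference between instruments. The Analysis Plan also foresees comparing pre-to-post changes between groups, so an item absent at baseline is lost to that comparison for good.

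**Working it through.** **Size of the survey.** Inputs from Statistical Power: 120 villages, 40 respondents each, 8 of the 40 high-risk.

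- Respondents per round: 120 × 40 = 4,800, as the protocol states.
- High-risk: 8 / 40 = 20%; 120 × 8 = 960, as the protocol states.

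**Salt effort: each survey item on salt.**

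- B.5: how often pickled food is eaten.
- B.6: what the person does when food is bland.
- B.7 to B.9: knowledge of harm, of what lowers blood pressure, and of recommended intake.
- D.1.1: whether the village doctor advised less salt; high-risk respondents only.

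None asks whether the respondent is trying to eat less salt. Items yielding the outcome: 0, so 0 of 4,800 respondents.

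The case management record cannot stand in. Under the factorial allocation, 30 villages get both interventions, 30 package only, 30 salt only and 30 neither. Records exist in 30 + 30 = 60 villages. The 30 salt-only and 30 neither villages have none. In the 60 that have them, only managed high-risk patients are covered, and the entries are made by doctors who are paid per patient when salt reduction and not smoking are both recorded (Appendix 1-C, indicator 4).

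**Regular management: each component against each source.**

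| Component | Survey (all villages) | Case record (60 package villages) |
|---|---|---|
| Monthly visits | C.6, yes/no | dated visit entries |
| Count against 9 in a year | not available | can be counted |
| Blood pressure at each visit | C.7, from never to every time | recorded at each visit |
| Cardiovascular medicine prescribed at each visit | not available; D.3 gives months on blood pressure drugs, D.3.1 and D.5.3 the prescriber | recorded at each visit |

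Two of the four components cannot be obtained from the only instrument used in both arms.

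**The visit rule.** Someone seen in 9, 10 or 11 of 12 months reaches the count of nine but has not been seen every month. The text does not say how to class that person, and C.6 cannot separate them from someone seen less often.

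**Medication items.** Section D is for high-risk respondents; the interview ends for everyone else. Not asked: 4,800 − 960 = 3,840 (80%). The 20% is a planning figure. At an assumed high-risk share of 15% the number is 4,080, and at 40% it is 2,880.

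**The case against.** The case for leaving this alone has several good parts.

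- **Regular management is not beyond computing everywhere.** A reader might infer that neither arm can supply it. The documents do not support that. In package villages the records hold visit dates, blood pressure and prescriptions for managed patients. A survey proxy can also be built from C.6, C.7 (every time), D.3 (its top category is nine months or more), D.3.1 and D.5.3. What fails is the definition as written, scored the same way in both arms.
- **The visit rule need not be a contradiction.** It can be read as a monthly schedule with nine visits as minimum attendance. Nor does a person seen in 9 to 11 months have to answer No to C.6, since the item is colloquial and some would say Yes. That is ambiguity, but it still leaves the outcome without a reproducible rule.
- **Salt effort has neighbours.** 24-hour urinary sodium and salt sales are listed, B.5 and B.6 are behavioural proxies, and the form is pre-printed 2010, so it must be reissued before follow-up. The item could be added then for a post-intervention comparison. This limits the damage but does not supply the listed outcome. The section on amendments defers details of the salt program, but the questionnaire is not on its list of deferred components.
- **Medication.** The sponsor's earlier trial reported that "withdrawal from medication was more pronounced in the salt substitute group than control group", and a reader might infer that a salt effect could be masked in 80% of the salt population. That does not follow. The 80% is the share not asked, and only people on treatment can withdraw from it. As an illustration, assume half of those skipped are hypertensive, 13% to 30.6% of these are treated (figures in the protocol's background and pilot sections), 10% net withdrawal (assumed) and 10 mmHg per drug (Statistical Power). The mean shift among those skipped is 0.5 × 0.13 × 0.10 × 10 = 0.07 mmHg to 0.5 × 0.306 × 0.10 × 10 = 0.15 mmHg, against a target of 2.5 mmHg. It scales in proportion to the assumed withdrawal. No listed salt outcome needs medication data, a change in medication is part of the intention-to-treat effect, and details of the economic evaluation are deferred.

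**Conclusion.** The point stands in two parts. First, the salt-effort outcome has no item in the survey: 0 of 4,800 respondents per round. Second, regular management cannot be scored to its definition alike in both arms, because the survey has no visit count and no item on prescribing at each visit, and the 60 villages without the package have no case records. The wording of the visit rule adds an unclassified group, those seen in 9 to 11 months.

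This assumes that Appendix 2 is used as shown and that the salt outcome refers to the surveyed older adults. The primary outcomes are untouched. The limit on Section D is an aid-to-interpretation issue only: about 3,840 of 4,800 are unobserved on the 20% assumption, which is not the number affected.

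**What to change.** Before the baseline survey, or at the latest before follow-up:

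1. Copy the three-level salt-effort item from Appendix 1-B into Section B and ask it of all respondents.
2. Replace C.6 with counts: in how many of the past 12 months the village doctor was seen, blood pressure was measured, and a cardiovascular medicine was prescribed.
3. State one threshold for scoring regular management, computed from the survey in both arms. This is a scoring rule for the outcome; the visit schedule in the package is a separate matter. Case records can then serve as supporting process data in package villages.
4. Optionally, ask D.3 of everyone, to help interpret the salt program's blood pressure effect.

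The cost is a few items, a minute or two per interview, and submission of the revised form to the ethics committees. If the change comes only at follow-up, the salt-effort item and the month counts support a post-intervention comparison but no comparison of changes from baseline.

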| D.3 How many months have you taken anti-hypertensive medication (AHM) during the past 12 months?  □1.≥9 months  □2.2-8 months  □3.＜2 months  □4 Not a long-term user  □5. Don’t know if have taken AHM  （if not a long-term user or don’t know, go to D.4） | | | | D.3.1Who prescribed the AHM?  □1. Buy by self  □2. TCM doctor  □3. Specialist  □4. Village doctor and specialist  □5. Village doctor | | | | | | | | D.3.3 Where do you but AHM?  □1. Village clinic  □2. Township center  □3. County hospitals  □4. Pharmacies | |
| D.3.2. Has village doctor adjusted the treatments, either dosage or number of AHM for you?  □1.Yes □0.No | | | | | | | | | |
| D.4 How many months have you taken aspirin during the past 12 months?  □1.≥9 months  □2.2-8 months  □3.＜2 months  □4 Not a long-term user  □5. Don’t know if have taken AHM  （if not a long-term user or don’t know, go to D.5） | | | | D.4.1 Who prescribed the aspirin?  □1. Buy by self  □2. TCM doctor  □3. Specialist  □4. Village doctor and specialist  □5. Village doctor | | | | | | | D.4.2 Where do you but aspirin?  □1. Village clinic  □2. Township center  □3. County hospitals  □4. Pharmacies | | |
| D.5 Have you taken any medication for your heart disease, stroke, diabetes or hypertension problems(s) during the past 1 month?   | □1.Yes □9.Don’t know | □0.No (if No, end survey) | | --- | --- |  | D.5.1 Medicine (brand name) | D.5.2 Use in all days?  (>25days in the last 30 days) | D.5.3 Prescribed by village doctor? | | --- | --- | --- | | 1. | □1.Yes □0.No | □1.Yes □0.No | | 2. | □1.Yes □0.No | □1.Yes □0.No | | 3. | □1.Yes □0.No | □1.Yes □0.No | | 4. | □1.Yes □0.No | □1.Yes □0.No | | 5. | □1.Yes □0.No | □1.Yes □0.No | | **（End of survey）** | | | | | | | | | | | | | | | | |
| Interviewer impressions: interviewee understands questions  □1Well □2Acceptable □3Does not understand | | | | | | | | | | | | | |
| Time of completion：**□□:□□**  Interviewer signature： | | | | | | | | | | | | | |

Date of quality review: 2010 __ month__ day time: **□□:□□**

Quality reviewer signature: _____________________

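### The Appendix 2 questionnaire cannot measure the 12-month village-doctor treatment outcome as the protocol defines it

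*Protocol*

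**What the plan says.** Under Secondary outcomes for the package intervention, the protocol counts a high-risk individual as a success if he or she attended the village clinic and "received pharmaceutical treatment from the village doctor at least once in the past year". The window is a year, one occasion is enough, and any drug qualifies.

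Under Outcomes evaluation, assessment is to be identical in all villages, and case management records are named as a source for the package only. The common source is therefore the population survey in Appendix 2. Its section D, for high-risk respondents, has these relevant items:

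- **D.1** dates the last village-doctor visit for the relevant conditions, then asks about lifestyle advice only.
- **D.3** asks "How many months have you taken anti-hypertensive medication (AHM) during the past 12 months". The answers are 9 months or more, 2 to 8 months, under 2 months, "Not a long-term user", and don't know. The routing note is "if not a long-term user or don’t know, go to D.4", which bypasses the prescriber question D.3.1.
- **D.4** has the same structure for aspirin, with the note "if not a long-term user or don’t know, go to D.5". This bypasses D.4.1, "Who prescribed the aspirin".
- **D.5** asks "Have you taken any medication for your heart disease, stroke, diabetes or hypertension problems(s) during the past 1 month". A No ends the survey. Otherwise each drug is listed and D.5.3 asks "Prescribed by village doctor".

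**The concern.** The outcome and the instrument differ in look-back period and in the drugs covered. A patient can meet the definition and leave no trace of it on the form.

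Two kinds of patient are at risk of being missed. The first took an antihypertensive or aspirin from the village doctor briefly, more than a month ago, and chose the fourth answer to D.3 or D.4 or did not know. The second took some other drug from the village doctor, such as a diabetes drug, and stopped more than a month before the survey.

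A comparison of arms on this outcome is biased if such patients are more common in one arm than in the other. That is plausible, because the package is built to change how often patients see and are treated by the village doctor.

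**Working it through.** The protocol states no rate, sample size or power for this outcome, so there is no figure to reproduce. The check has two parts.

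**1. Trace the form against the definition.**

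| Village-doctor treatment in the past year | Answer given | Prescriber recorded? |
|---|---|---|
| Any drug, taken in the past month | D.5 Yes | Yes, D.5.3 |
| Antihypertensive or aspirin, 2 months or more, stopped over a month ago | 9 months or more, or 2 to 8 months | Yes, D.3.1 or D.4.1 |
| Antihypertensive or aspirin, under 2 months, stopped over a month ago | Under 2 months | Yes, D.3.1 or D.4.1 |
| The same patient | Fourth option, or don't know | No |
| Any other drug, stopped over a month ago | No item applies | No |

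Rows three and four describe the same patient. Which row applies depends on how the respondent reads the options, because the form gives no rule separating them.

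D.3 and D.4 also have no answer for someone who never took the drug, so never-users and occasional users can share the fourth option. No later scoring rule repairs this. Coding that group as untreated misclassifies some treated patients, and coding it as missing discards people who really were untreated.

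**2. Effect on the between-arm difference.** For control (c) and package (p) villages, let R be the share whose village-doctor treatment the form captures, O the share with occasional-only treatment, and m the fraction of O that is missed. Assume that missed patients count as untreated and that m is the same in both arms.

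- True difference = (R_p + O_p) − (R_c + O_c)
- Observed difference = [R_p + (1 − m)O_p] − [R_c + (1 − m)O_c]
- Bias = observed − true = m × (O_c − O_p)

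All rates below are assumptions, with m = 1:

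- **A. Package turns occasional into regular treatment.** R_c = 30%, O_c = 20%, R_p = 50%, O_p = 10%. True: 60 − 50 = 10 points. Observed: 50 − 30 = 20. Bias +10.
- **B. Occasional treatment equally common.** R_c = 30%, R_p = 50%, O = 15% in both arms. True: 65 − 45 = 20. Observed: 50 − 30 = 20. Bias 0.
- **C. Package turns untreated people into occasional users.** R_c = 30%, O_c = 10%, R_p = 45%, O_p = 20%. True: 65 − 40 = 25. Observed: 45 − 30 = 15. Bias −10.

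With m = 0.5 the biases halve to +5, 0 and −5 points. An item that captures all occasional treatment makes m = 0 and removes the bias in every case.

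**The case against.** The strongest reply is that the form does better than a quick reading suggests. D.3 and D.4 look back 12 months, and respondents with 2 to 8 months or under 2 months of use do reach the prescriber question. These are the two drug classes named in the other package outcomes. This stands: it is wrong to say that prescribing is recorded only for long-term users. A two-week antihypertensive course five months ago can be captured if the respondent answers under 2 months.

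A reader might also infer that the one-month window misses 11/12, or 92%, of occasional treatment. With occasional-only treatment in an assumed 10, 20 or 30% of control patients, the control proportion would be 9, 18 or 28 points too low. The protocol does not support this. The calculation ignores the 12-month route through D.3 and D.4, and the prevalences have no source in the document. Even for D.5 alone, 1/12 describes a momentary treatment: a 14-day course overlaps a 30-day window about (30 + 14)/365 = 12% of the time.

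Nor does the protocol state that skipped items score as No. That rule may sit in an analysis plan that is not shown. As set out above, though, no rule can separate the mixed group.

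Could another source fill the gap? Case management records cannot serve control villages. The economic evaluation mentions patient interviews on medication use, but its details are still to be submitted and nothing links them to this outcome. The questionnaire is not on the protocol's list of components still to be determined.

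Finally, this is one of eight secondary package outcomes. The primary outcome and its power calculation do not depend on it.

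**Conclusion.** The form does not measure this outcome as defined, in either arm. Some qualifying treatment will go unrecorded, and how much cannot be worked out from the protocol.

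A reader might conclude that the package effect is overstated. That is plausible. The background describes village-level cardiovascular control as largely absent, while Appendix 1-B requires monthly records and Appendix 1-C pays per monthly follow-up. Both favour regular treatment, which the form captures.

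The protocol also gives reasons for the opposite sign. The power section expects only about half of high-risk patients to be managed, identification is opportunistic, and the payment scheme foresees patients with too few monthly records. The package could therefore create occasional users and have its effect understated.

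The supportable conclusion is a possible bias of m × (O_c − O_p), from +10 to −10 points in the assumed scenarios, with unknown size and direction. It rests on missed patients being counted as untreated and on equal m in both arms. The blood pressure outcome is not affected. The point is worth fixing because the remedy is cheap and no analysis can replace it.

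**What to change.** At the follow-up survey, in all villages, add one item directly after D.1 for every high-risk respondent, with no skip: *In the last 12 months, did your village doctor prescribe or give you any medicine for these problems at a clinic visit? Yes / No*. Count those who never visited as No. Derive the outcome from this item alone and compare the arms after the intervention.

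In D.3 and D.4, add a separate answer for never having taken the drug, and state how under 2 months differs from the fourth option.

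The cost is one yes/no question and two edited answer lists. The form carries a preprinted 2010 date and the follow-up survey is scheduled for November 2012 to January 2013, so it needs reissuing anyway. If the baseline survey is already complete, the new item has no baseline value. The net pre-post comparison in the Analysis plan is then unavailable for this outcome, but the post-intervention comparison, which the Analysis plan also specifies, remains. The changed answers to D.3 and D.4 will also match the baseline form less exactly. Merging the never and fourth options restores most of that match.
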